### Relevant Concomitant Care and Interventions That Are Permitted or Prohibited During the Trial

To participate, veterans need to be stable (no changes in the last 30 days) on medications prescribed for a mental health disorder. Veterans randomized to either treatment group are allowed to start or continue any nonstudy treatment resources, including mental health treatment, during their participation in the trial.

### Participant Timeline

Figure 2 shows the participant timeline in detail.

**Figure 2 figure2:**
[figure not shown]
Participant timeline.

### Outcomes

In aim 1, qualitative veteran feedback on the Deprexis intervention and study procedures will be obtained; no quantitative analyses will be completed. Broadly, the posttreatment interview questions will cover the following content areas: (1) motivation toward, and barriers to, treatment and participation in the study; (2) Deprexis content, presentation, adherence, and usability; (3) perceptions of study procedures; and (4) changes experienced in mood, behavioral engagement, or interpersonal interactions after Deprexis treatment.

In aim 2a, we will test whether Deprexis is effective for decreasing depressive symptoms and improving functional outcomes in veterans presenting for VA health care with mild to moderate depressive symptoms. The primary outcomes for this aim are depressive symptoms (assessed with the QIDS-SR-16) and functioning (assessed with the World Health Organization Disability Assessment Schedule II [WHODAS-II] and the Sheehan Disability Scale [SDS]). The secondary outcomes are other psychopathology (assessed with the PTSD Checklist for Diagnostic and Statistical Manual of Mental Disorders, Fifth Edition [PCL-5] and the PDSQ), social functioning (assessed with the Interpersonal Support Evaluation List–Short Form [ISEL-SF] and the Inventory of Interpersonal Problems–Short Circumplex Form [IIP-SC]), and quality of life (assessed with the Quality of Life Scale [QLS]).

Exploratory analyses in aim 2b will examine whether demographic variables (sex, gender, age, race, ethnicity, and education), PTSD symptom severity (assessed with the PCL-5), comorbidity (assessed with the PDSQ), treatment credibility (assessed with the Credibility and Expectancy Questionnaire), frequency of study support, and Deprexis use moderate treatment effects.

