### Sample Size

#### Aim 1

In determining the sample size for qualitative studies, the key goals are to develop case-oriented perspectives, select participants with a range of characteristics and perspectives, and achieve saturation (ie, the point at which subsequent interviews fail to produce new themes) [56]. Research indicates that typically, saturation is reached with 12 to 16 interviews. As we are also obtaining qualitative data on veterans who did not adhere to the treatment (approximately 23% of the sample), we increased our recruitment target slightly to 16 to 20 veterans to allow for a sufficient sample of veterans who completed Deprexis treatment, as well as those who terminated treatment early (ie, did not complete the posttreatment or follow-up questionnaires).

#### Aim 2

Effect sizes in the general population Deprexis RCT for participants with mild to moderate depression (QIDS-SR-16 score <21) ranged from Cohen *d*=0.65 to Cohen *d*=0.90. Some evidence suggests that effect sizes for psychological interventions may be smaller for veterans [57]; therefore, we estimate that effect sizes are at least medium (Cohen *d*=0.50) for measures of functioning and large (Cohen *d*=0.80) for depressive symptoms. To achieve 0.8 power at an α of .05, a total of 102 participants need to be recruited. Accounting for 23% attrition over time, we will randomize 132 participants at baseline. In the general population trial, approximately 57% (n=213) of the randomized participants were high engagers (>90 min), and effect sizes were slightly higher in the high engager group (Cohen *d*>0.67) than in the overall sample. Thus, we expect to be adequately powered for analysis in this subgroup.

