#### Methods for Additional Analyses

In an exploratory and hypothesis-generating mode, potential moderators for Deprexis treatment effects will be examined. Generalized linear mixed models with robust maximum likelihood estimation will be used to model continuous outcomes (eg, changes in psychosocial functioning outcomes and depressive symptoms), and logistic models will be used to model changes in dichotomous outcomes (eg, significant change: ≥50% improvement in scores) over time. *Participant* will be entered as a random effect (ie, random intercepts). Each potential moderator will be examined in a separate model for changes in primary outcomes (QIDS-SR-16, WHODAS-II, and SDS). Each model will include main effects for the potential moderator and time (before treatment, after treatment, and follow-up), 2-way interactions (moderator×time and time×treatment condition), and a 3-way interaction (moderator×time×treatment condition). To prevent spurious associations, the α value will be Bonferroni corrected [65]. A variable will be considered a moderator of treament effects if there is a significant 3-way interaction (moderator×time×treatment condition) after treatment or at 8-week follow-up.

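### Three unranked primary outcomes are each tested at an unadjusted .05 with no success rule, while only exploratory tests are corrected: claiming efficacy on any one carries about 8% to 14% error, not 5%

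*Protocol article*

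**What the plan says.** - **Outcomes.** For aim 2a, "The primary outcomes for this aim are depressive symptoms (assessed with the QIDS-SR-16) and functioning", with functioning measured by both WHODAS-II and SDS. Methods for Additional Analyses repeats the list as "changes in primary outcomes (QIDS-SR-16, WHODAS-II, and SDS". None of the three is ranked above the others.
- **Aims.** The hypothesis covers functioning and depressive symptoms together. It does not say what pattern of results counts as success.
- **Sample Size, Aim 2.** "To achieve 0.8 power at an α of .05, a total of 102 participants need to be recruited". The assumed effects are that "effect sizes are at least medium (Cohen *d*=0.50) for measures of functioning" and "large (Cohen *d*=0.80) for depressive symptoms". Then: "Accounting for 23% attrition over time, we will randomize 132 participants at baseline". The α is given once, without sidedness and without division among outcomes.
- **Statistical Methods.** For each continuous outcome, a mixed model with condition, three time points and their interaction is compared with the model without the interaction, and that comparison is the significance test. One-tailed Welch tests are added for comparisons within a time period. No adjustment is mentioned.
- **Methods for Additional Analyses.** For the moderator models: "To prevent spurious associations, the α value will be Bonferroni corrected".
- **Analysis populations.** Aim 2 is analysed in four groups (intention-to-treat, per-protocol, high-engagement, completer), and none is named as primary.

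**The concern.** The article sets a multiplicity policy, but it protects the hypothesis-generating analyses and leaves the confirmatory ones unprotected. With three primary outcomes, no order and no success rule, a significant result on any one could be reported as efficacy, and that claim would not carry a 5% error rate. The trial is unblinded and every outcome is self-reported, so a rule fixed in advance is one of the few safeguards available. The sample size made no allowance for three tests, so a correction chosen late could cost power that nobody planned for.

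**Working it through.** **Inputs from the article.** Three primary outcomes; one interaction test each; α=.05; power 0.80; d=0.50 (functioning) and d=0.80 (depressive symptoms); 102 evaluable, 132 randomised 1:1, 23% attrition. **Assumed:** correlation among the three outcomes, 0 to 0.9.

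**1. Reproduce the plan's figure.** Per arm, n = 2(z₁₋α + z₀.₈₀)²/d².
- One-sided .05, d=0.50: 2(1.645+0.842)²/0.25 = 49.5, so 50. The t-based solution is 50.15, so 51 per arm and **102 in total**, as stated.
- Two-sided .05: 2(1.960+0.842)²/0.25 = 62.8, so 63. The t-based solution is 64 per arm, or 128, which does not match.
- Attrition: 102/0.77 = 132.5, against 132 stated.

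So 102 corresponds to one d=0.50 test at an undivided one-sided .05.

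**2. Familywise error, three interaction tests at .05, all null.** If independent, 1 − 0.95³ = 1 − 0.8574 = 0.143. For correlated outcomes, I simulated three correlated 2-df statistics (three time points give two interaction terms), each compared with the .05 chi-square cut-off.

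| Assumed correlation | Chance of at least one false claim | Multiple of 5% |
|---|---|---|
| 0 | 14.3% | 2.9 |
| 0.5 | 12.7% | 2.5 |
| 0.7 | 11.1% | 2.2 |
| 0.8 | 10.0% | 2.0 |
| 0.9 | 8.5% | 1.7 |

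With single-contrast two-sided tests instead, the value at 0.9 is about 8.4%.

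**3. Cost of plain Bonferroni (.05/3 = .0167) at 51 per arm, d=0.50.** Power falls from 0.81 to 0.64 one-sided, or from 0.71 to 0.54 two-sided. Restoring 80% would take 144 evaluable (188 randomised) one-sided, or 172 (224) two-sided.

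**4. Cost of a fixed sequence at two-sided .05, 51 per arm, planned effects.**
- QIDS-SR-16 (d=0.80): 0.98.
- WHODAS-II (d=0.50), reached and significant: about 0.70, against 0.71 tested alone.
- SDS (d=0.50), reached and significant: about 0.53 at outcome correlation 0.3, rising to 0.61 or 0.62 at 0.8, depending on the approximation.

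The fall from 0.81 to 0.71 for a functioning measure comes from two-sided testing, not from the sequence. These powers use the same simple two-group comparison as the sample size, not the mixed model itself.

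**The case against.** **The hypothesis may be a joint one.** Aims links functioning and depressive symptoms, and if all three outcomes had to succeed, no adjustment of α would be needed. That is correct, but the article does not state such a rule. The inflation is therefore conditional on an any-one-succeeds claim, which the article neither adopts nor rules out.

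**Success rules and testing order are often left to an analysis plan, which is not shown.** This limits the point, since such a plan could add a procedure. It does not remove it: the article itself fixes the α, the sample size, the confirmatory tests and a correction, and reserves that correction for the exploratory family. The moderator models are a separate family, so this is no formal contradiction, but it is a poor allocation of protection.

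**The article never says .05 applies to each outcome.** True. It gives one α and no division, and using it undivided for each test is the natural reading.

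**A stronger reading is tempting: six tests, three outcomes at two visits.** If all were independent, the error would be 26.5%. One-sided, with outcome correlations 0.5 to 0.8 and visit correlations 0.3 to 0.7, it would be 14.4% to 21.1%. The article does not support this as the primary analysis, because the stated significance test is one likelihood ratio comparison per outcome across all time points. Those figures would apply only if the within-visit Welch tests were used to support claims, and their status is not stated. For the same reason, the absence of a named primary visit carries little weight.

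**A depression-first order sits awkwardly with the trial's emphasis on functioning.** This is fair. The order is the sponsor's choice.

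**Conclusion.** The concern holds in a bounded form. Three primary outcomes, one interaction test each, have no adjustment, order or success rule, while the only stated correction covers exploratory tests. Under an any-one-succeeds claim the familywise error is about 8% to 14%: at least twice nominal for correlations up to about 0.8, and 1.7 times at 0.9. WHODAS-II and SDS both measure disability, so the lower part of the range is plausible for that pair. The result rests on assumed correlations and on all three null hypotheses being true.

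A reader might also infer that Bonferroni would cut power from the planned 80% to 54%. That mixes two changes: on the one-sided basis that reproduces 102, the fall is from 0.81 to 0.64; two-sided, it is from 0.71 to 0.54. The gap should be closed, and it needs no redesign.

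**What to change.** State in Statistical Methods that the confirmatory analysis is in the intention-to-treat population and tests treatment×time in a fixed sequence, each at .05: for example QIDS-SR-16, then WHODAS-II, then SDS, with confirmatory claims ending at the first non-significant result. Another order, Holm, or a declared rule that all three must succeed would serve equally well for error control. Label the within-visit one-tailed Welch tests and the other three analysis groups as supportive.

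**Cost.** Wording only; the article reports 4 participants recruited and analysis expected in June 2029. The sequence is not free:
- Functioning claims become conditional on QIDS-SR-16, and SDS also on WHODAS-II, giving the step 4 powers of about 0.98, 0.70 and 0.53 to 0.62.
- The all-must-succeed rule has the same 0.53 to 0.62 as its overall power, because the last step of the sequence is reached and passed only when all three are significant.
- Holm avoids ranking the outcomes but starts at .05/3 for the smallest p-value.

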### Aims

Deprexis has not yet been rigorously evaluated with a veteran population in a VA medical center setting. This study aims to fill this critical gap in the literature by testing whether Deprexis is acceptable and effectively decreases depressive symptoms and improves functional outcomes in veterans (N=152) presenting for VA health care with mild to moderate depressive symptoms. The objective of aim 1 is to assess perceptions, needs, and preferences as they relate to Deprexis through conducting posttreatment assessment interviews with veterans (n=16-20) and identify the components that improve veterans’ experience and uptake of Deprexis. The results obtained in aim 1 will be used to inform the rollout of RCT procedures under aim 2. Aim 2a involves completing an RCT comparing an 8-week course of Deprexis to a treatment-as-usual (TAU) control condition. We hypothesize that veterans engaged in Deprexis will show improvements on measures of functioning and decreases in depressive symptoms compared to the TAU control group. To generate hypotheses for future study, the objective of exploratory aim 2b will be to examine whether demographic variables, baseline psychopathology, credibility, and Deprexis use moderate treatment effects on the primary outcomes.

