### Strategies to Improve Adherence to Intervention Protocols

Adherence will be optimized using strategies from previous Deprexis trials. All veterans will be sent brief SMS text messages to increase engagement. These SMS text messages will target behavioral and cognitive processes that are known to maintain depressive symptoms and will include reminders to use the Deprexis program. Research staff will also have access to veterans’ real-time Deprexis use data, and based on this use data, short encouraging emails will be sent to them by research staff. These emails will range from acknowledging the veterans’ use of the Deprexis program to encouraging further engagement and addressing feelings of discouragement. Research staff will also reach out to veterans who have not activated their free Deprexis vouchers to provide technical support if needed. Study staff will initiate contact with veterans if there is no engagement with Deprexis over a 2-week period.

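### The three-way interaction rule cannot test Deprexis use as a moderator, because use does not vary in the control arm; study support either shares this problem or, being post-randomization, cannot be read as moderation

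*Protocol article*

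**What the plan says.** The Aims section includes use among the exploratory moderators: it asks whether demographic variables, baseline psychopathology, "credibility, and Deprexis use moderate treatment effects on the primary outcomes". The Outcomes section repeats this and adds study support: "frequency of study support, and Deprexis use moderate treatment effects".

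Methods for Additional Analyses gives one procedure for all of them. "Each potential moderator will be examined in a separate model for changes in primary outcomes". On content, "Each model will include main effects for the potential moderator and time", together with "2-way interactions (moderator×time and time×treatment condition), and a 3-way interaction (moderator×time×treatment condition". The decision rule is: "A variable will be considered a moderator of treament effects if there is a significant 3-way interaction", judged after treatment or at follow-up. No exception is made for use or support, and no within-arm analysis is described for either.

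The end of the Intervention Description section gives the control arm standard VA resources and a list of them. It mentions no voucher, delayed access or use measurement for that arm.

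Strategies to Improve Adherence to Intervention Protocols describes the support. Staff see use data and "based on this use data, short encouraging emails will be sent to them by research staff". They also help veterans whose vouchers are not activated and make contact after two weeks without engagement. The same section words the text messages as going to every veteran, and Plans to Promote Participant Retention describes reminders and calls without limiting them to one arm. The article does not define how the frequency of study support is counted.

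**The concern.** A three-way interaction asks whether the arm difference in change depends on the moderator. That requires the moderator to vary in both arms. Deprexis use varies only in the arm that receives Deprexis, so the control arm says nothing about how change would differ across levels of use. The stated rule then has no test behind it for a variable named in the aims.

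The practical risk is in what happens when the model is fitted. Software may drop the redundant columns or fail. If the analyst removes use×time to make the model run, the coefficient that remains is the slope of outcome on use within the Deprexis arm. That describes a behaviour chosen after randomization. Reported under the stated rule, it would look like moderation of a randomized effect.

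**Working it through.** The plan gives no figure for this point, so the check is whether the stated term can be estimated.

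**Inputs.** 132 participants randomized 1:1 (Trial Design), so 132/2 = 66 per arm. Three time points, hence two post-baseline contrasts. Terms as listed in Methods for Additional Analyses.

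**Model.** Let M be the moderator, g = 1 for Deprexis and 0 for TAU, and T1, T2 the indicators for posttreatment and follow-up. With pretreatment as reference, the listed terms give the intercept (1), M (1), time (2), M×time (2), time×g (2) and M×time×g (2): 1+1+2+2+2+2 = 10 columns.

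**Algebra.** Suppose M equals a constant k for everyone in TAU. Then for each T,

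M×T×g = M×T − k×T + k×T×g.

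Every term on the right is already in the model. With k = 0 the three-way column equals M×T exactly. Centring only changes k.

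**Numerical check.** Rank of the fixed-effects matrix with and without the three-way columns; the difference is the degrees of freedom for the deciding test.

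| Coding of M | Columns | Rank | Rank without three-way | df for three-way |
|---|---|---|---|---|
| Use, 0 in TAU | 10 | 8 | 8 | 0 |
| Use, grand-mean centred | 10 | 8 | 8 | 0 |
| Use, 0 in TAU, with condition and M×condition added | 12 | 9 | 9 | 0 |
| Support, 0 or another constant in TAU | 10 | 8 | 8 | 0 |
| Support, varying in TAU | 10 | 10 | 8 | 2 |
| Baseline moderator, varying in both arms | 10 | 10 | 8 | 2 |

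If use is coded as missing in TAU, only the Deprexis arm remains. The rank is 6 of 10 and there is no condition contrast.

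**Dependence on coding.** The listed terms contain no condition main effect and no M×condition. Some formula software then gives time×g and M×time×g one column per visit, including pretreatment: 1+1+2+2+3+3 = 12 columns. For use, the rank is 9 with or without the three-way columns, so the result is again 0 df. For a true baseline moderator, the same software yields three three-way columns, where moderated change has two. The finding on use is therefore independent of coding; the content of the test for the other moderators is not.

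**The case against.** The case for leaving the text alone is that aim 2b is labelled exploratory and hypothesis-generating, with a Bonferroni correction. Engagement is also examined through the analysis groups defined by at least 60 and at least 90 minutes of use. A term that cannot be estimated would come to light when the model is fitted. This limits the harm, and I accept it as a limit on severity. It does not supply the missing test: those groups are analysis populations, not a moderation rule.

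Three stronger readings are tempting, and the documents do not support them.

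- A reader might infer that study support is certainly untestable too. The variable is undefined. The text messages are worded as going to all veterans, and the retention contacts are not restricted by arm. If such contacts count and vary in TAU, the term keeps its 2 df. Nor is all support triggered by use: the text messages are not. What stands is that support accrues after randomization and is partly triggered by use or non-use.
- A reader might infer that omitting condition and moderator×condition spoils the test for every baseline moderator. With pretreatment as reference, the listed terms give a proper 2-df test and a model that constrains the arms to equal baselines, a recognised choice in a randomized trial. The main aim 2 model in Statistical Methods does enter condition, so the list may simply be condensed. The wording leaves the coding open; it does not establish that baseline imbalance enters the test.
- A reader might take 12 columns and rank 9 as a property of the stated model. That holds only under one coding. Baseline-reference coding gives rank 8 of 10. Only the 0 df for use is common to both.

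**Conclusion.** The point holds for Deprexis use. The deciding term has 0 of the 2 expected degrees of freedom for each of the three primary outcomes (QIDS-SR-16, WHODAS-II and SDS), so aim 2b cannot be answered for use by the stated rule. This is exact aliasing, not low power.

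For frequency of study support the conclusion is conditional. Under the Deprexis-directed definition it fails in the same way. Under a wider definition it is estimable but is not moderation of the randomized effect.

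The result assumes that no use is recorded in TAU, which is what the described voucher access and control condition imply. The primary comparison, the secondary outcomes and the sample size are unaffected.

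**What to change.** In Methods for Additional Analyses:

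- Take Deprexis use and frequency of study support out of the three-way moderator test, and align the lists in Aims and Outcomes.
- Analyse both as dose-response associations within the Deprexis arm, labelled non-causal, and define which contacts count as study support.
- Keep the three-way test for baseline variables measured in both arms. State that the deciding test is the 2-df moderator×time×condition term for change from baseline, so that the result does not depend on software coding.

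The cost is wording only; data collection and sample size do not change. The downside is that two variables move from moderation to descriptive within-arm analysis.

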### Measures

The following primary outcomes (assessed at all time points) are administered through Qualtrics:

The QIDS-SR-16 [31] is a 16-item self-report measure of depressive symptom severity. This measure takes 5 to 7 minutes to complete and assesses the 9 Diagnostic and Statistical Manual of Mental Disorders, Fourth Edition (DSM-V), symptom criterion domains for depression (eg, “There is no change in my usual appetite”) and has been shown to be highly internally consistent (Cronbach α=0.86). The QIDS-SR-16 demonstrates concurrent validity with measures assessing similar outcomes (*r*=0.86-0.65) and is sensitive to symptom change [31]. Scores of >6 are indicative of meaningful depressive symptoms. The QIDS-SR-16 will serve as a primary eligibility criterion, specifically a QIDS-SR-16 score between 6 and 20. To verify the duration of depressive symptoms, we will include an item adapted from the Clinical Interview Schedule–Revised, which will assess the duration of depressive symptoms on a 6-point scale.

The WHODAS-II [35] is a 36-item self-report questionnaire, which takes 5 to 20 minutes to complete. The measure assesses functional disability across 7 domains: understanding and communicating, getting around, getting along with people, life activities, work, participation in society, and self-care (eg, “In the last 30 days, how much difficulty did you have in concentrating and doing something for 10 minutes?”). The WHODAS-II total score is scaled from 0 to 100, with higher scores indicating greater disability. The WHODAS-II has high test-retest reliability (*r*=0.98) and moderate to good concurrent validity with measures assessing similar outcomes (*r*=0.45-0.65), and it is sensitive to change in functional disability after treatment [35].

The SDS [36] is a 3-item self-report measure of symptom-related disability (eg, “The symptoms have disrupted your work/school life”) that has been used in previous Deprexis trials. The SDS takes approximately 5 minutes to complete, and items are summed (range 0-30), with higher scores indicating greater disability. The SDS was developed as a global measure of the impact of mental illness on work and school activities, family relationships, and social functioning. The SDS is highly internally consistent (Cronbach α=0.89) and has good reliability (*r*=0.73and high construct validity [37]; in addition, it is sensitive to treatment effects [38].

The secondary outcomes listed in the following sections are assessed at all time points.

The PDSQ [32] is a 125-item questionnaire containing 13 subscales (eg, MDD, anxiety disorders, and alcohol and drug abuse and dependence) that is used to screen for symptoms of mental health disorders. The PDSQ takes 15 to 20 minutes to complete, with scoring and cutoffs varying by individual scale [34]. This scale shows high internal consistency (Cronbach α=0.82); high test-retest reliability (*r*=0.84); and good discriminant, convergent (mean *r*=0.17), and concurrent (mean *r*=0.72) validity [32].

The BDI-II [34] is a 21-item self-report measure assessing depression symptom severity, completed in approximately 10 minutes. Items are scored on a 4-point scale (range 0-63), with higher scores reflecting increased endorsement of depressive symptoms. A score of ≥15 indicates the presence of clinically significant depressive symptoms [39]. The BDI-II has high internal consistency (Cronbach α=0.90), good to high test-retest reliability (*r*=0.73-0.96), and it correlates highly with interview-based measures of depression (*r*=0.66-0.75) [40]. The BDI-II will be used as a secondary measure of depression and to assess the suicidal ideation exclusion criteria.

The IIP-SC [41] is a 32-item self-report measure assessing the interference of depressive thoughts, behaviors, and symptoms across various psychosocial domains (eg, “It is hard for me to join in on groups”). The measure takes 10 to 15 minutes to complete. It consists of 8 scales consisting of 4 items each. Scores are averaged (range 0-4), with higher scores indicating greater interpersonal problems. The IIP-SC is sensitive to treatment effects and has demonstrated good to high internal consistency (Cronbach α=0.64-0.87) and good to high test-retest reliability (*r*=0.56-0.81) [42].

The ISEL-SF [43] is a 12-item self-report measure assessing perceived social support across four subscales: (1) appraisal support (the perceived availability of someone to discuss issues of personal importance), (2) tangible assets support (the perceived availability of material aid), (3) belonging support (the perceived availability of others to interact with socially), and (4) self-esteem support (the perceived availability of others with whom one compares favorably). The measure takes approximately 5 minutes to complete, with higher scores indicating the presence of increased social support. There is evidence that perceived social support improves after internet-delivered interventions for depression [44]. The ISEL-SF has been found to be highly internally consistent (Cronbach α=0.83) and has demonstrated moderate convergent construct validity with other measures of social support (*r*=0.45) [45].

The QLS [46] is a 16-item self-report measure of quality of life across various domains, including material and physical well-being; relationships; social, community, recreational, and civic activities; personal development; and fulfillment and independence. Ratings for domains (eg, “Health, being physically fit, and vigorous”) are assigned on a 7-point scale from “delighted” to “terrible” (range 12-116), with higher scores indicating a better quality of life. The measure takes approximately 10 minutes to complete. The QLS has high to excellent internal consistency (Cronbach α=0.82-0.92) and high test-retest reliability (*r*=0.78-0.84), and it has demonstrated good convergent validity with similar measures (*r*=0.67-0.75) [47]. Furthermore, the QLS is able to discriminate between populations with expected differences in quality of life (ie, those with chronic illness and those without) [48].

The PCL-5 [49] will be used to identify whether PTSD is a potential moderator of symptom change and to examine whether Deprexis produces meaningful changes in PTSD symptoms. The version of the PCL-5 used (PCL-5 with Criterion A) will include an assessment of the presence of a traumatic event meeting criterion A (the first criterion for diagnosing PTSD according to the Diagnostic and Statistical Manual of Mental Disorders, Fifth Edition). If no traumatic event is endorsed, veterans will not complete the remaining PCL-5 questions. Veterans who endorse exposure to a criterion A traumatic event will complete the 20-item PCL-5, which assesses PTSD symptom severity on a 5-point scale (eg, “In the past month, how much were you bothered by ‘Repeated, disturbing, and unwanted memories of the stressful experience?’”). Scores range from 0 to 80, with scores of >31 being indicative of probable PTSD (ref). The measure takes approximately 10 minutes to complete. The measure has excellent internal consistency (Cronbach α=0.94), high test-retest reliability (*r*=0.82) [49], and moderate convergent and discriminant validity (*r*=0.31-0.60) [49]. The PCL-5 is as sensitive to clinical change that occurs between pre- and posttreatment assessments as gold standard interview-based measures of PTSD symptoms (alerting convergent validity: *r*=0.94 and contrast converting validity: *r*=0.92) [50].

The following moderators and covariates are measured at baseline:

The Credibility and Expectancy Questionnaire [51] is a 6-item self-report survey used to measure participants’ perceived treatment expectancy and the credibility of clinical outcome studies (eg, “At this point, how logical does the course offered to you seem?”). The measure takes approximately 5 minutes to complete, with higher scores indicating increased treatment credibility. Treatment credibility predicts therapy outcome [52] and was an important predictor of Deprexis treatment response in the general population RCT [53]. The measure has high internal consistency (Cronbach α=0.84) and high test-retest reliability (*r*=0.83) [52].The Client Satisfaction Questionnaire-8 [54] will be administered after treatment to assess the quality of services, treatment satisfaction, and willingness to recommend the treatment to others (eg, “How would you rate the quality of service that you received?”). The self-report measure takes approximately 5 minutes to complete and consists of 8 items scored on a 4-point scale (range 4-32), with higher scores representing greater acceptability. The measure has high internal consistency (Cronbach α=0.91), and it has been shown to correlate with treatment attendance (*r*=0.54) and outcomes (*r*=–0.35) [55].Participants will self-report on demographic variables, including sex, gender, race, age, ethnicity, marital status, employment, and income. The demographic questionnaire will take approximately 10 minutes to complete.

